## Abstract

**Introduction:**

Parkinson’s disease (PD) is the second most common, progressive, and debilitating neurodegenerative disease associated with aging and the most common movement disorder. Photobiomodulation (PBM), the use of non-thermal light for therapeutic purposes using laser or light emitting diodes (LED) is an emerging non-invasive treatment for a diverse range of neurological conditions. The main objectives of this clinical trial are to investigate the feasibility, safety, tolerability, and efficacy of a novel transcranial LED helmet device (the “PDNeuro”) in the alleviation of symptoms of PD.

**Methods and analysis:**

This is a 24-week, two-arm, triple-blinded randomized placebo-controlled clinical trial of a novel transcranial “PDNeuro” LED Helmet, comparing an active helmet to a sham helmet device. In a survey, 40 PD participants with Hoehn and Yahr Stage I–III during ON periods will be enrolled and randomly assigned into two groups. Both groups will be monitored weekly for the safety and tolerability of the “PDNeuro” LED Helmet. Clinical signs and symptoms assessed will include mobility, fine motor skills and cognition, with data collected at baseline, 12 weeks, and 24 weeks. Assessment tools include the TUG, UPDRS, and MoCA all validated for use in PD patients. Patient’s adherence to the device usage and participant drop out will be monitored weekly. At 12 weeks both placebo and treatment groups will crossover and placebo participants offered the treatment. The main indicator for clinical efficacy of the “PDneuro” Helmet is evidence of sustained improvements in motor and non-motor symptoms obtained from participant self-reported changes, carer reporting of changes and objective reassessment by the investigators. The outcomes will assist in a future larger randomized trial design.

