**FIGURE 2 F2:**
[figure not shown]
PDNeuro lateral view.

This triple blinded, randomized controlled, at-home 24-week trial (RCT) with a crossover of the placebo group, has been designed to test the safety and effectiveness of the “PDNeuro” Helmet device in modifying clinical signs and symptoms experienced by PD patients. This compliments a previous experimental study that showed efficacy of a combined treatment protocol (transcranial with an abdominal, neck, and nasal application) in PD patients (Liebert et al., 2021). In previous published studies, the authors have demonstrated observable changes after 4-weeks of intervention, with statistical significance reported at 12-weeks utilizing both transcranial and remote PBMt, suggesting that 24-weeks will be sufficient to demonstrate significant effects with the present study being a randomized controlled trial with increased total number of participants (Liebert et al., 2021).

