## Methods and analysis

### Trial design

The study is a 24-week, two-arm, triple blinded randomized placebo-controlled trial evaluating the safety and effectiveness of the “PDNeuro” Helmet (see Figures 1, 2) compared with a sham helmet device. Treatment will consist of PBMt to the head six times per week for 12 weeks (see Figure 3), with Group 1 (the active group) receiving 12 min of infra-red and 12 min red LED, and Group 2 (the sham group) receiving sham treatment for 24 min. After the initial 12 weeks, the sham patients will be given the active treatment for 12 weeks while the active treatment group will have a 12 weeks washout period and then be re-assessed in 12 weeks (see Figure 3). Outcome measures will be collected by the study investigators that have received specialized training in assessment and data collection.

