### Outcome measures

Due to the broad clinical signs and symptoms of PD, a range of outcome measures were selected to determine functional improvement (Table 1). Many PD clinical rating scales have been developed since the 1960s that assess both motor and non-motor functions (Ramaker et al., 2002) and all outcome measures to be used in this study have been validated for use in PD remotely (Abdolahi et al., 2013; Stillerova et al., 2016). The primary outcome measures will be conducted and recorded using a combination of self-reported assessment and visual assessment obtained *via* Zoom video link. Outcome measures will be supervised, and data will be collected *via* specialist examiners and physiotherapists all trained in conducting each assessment. Outcome measures will be obtained at baseline, 12-week and 24-week intervals (see Figure 3).

**TABLE 1 T1:** Outcome measurements.

Primary outcome measurements	Data collection tools
1. Safety of PDNeuro helmet device	24-h access to health personnel Weekly [or as needed] technical meetings
2. Motor assessment	MDS-UPDRS [Modified Part 3 Motor component]
3. Social experiences and difficulties	PDQ39

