### Data collection

Once accepted on the trial all data will be stored in a secure location both in paper and electronic form. Data collected will include patient’s sociodemographic data and clinical history. Next, the primary outcomes and the secondary outcomes of the study will be collected. At the end of 12 weeks, the primary and secondary outcomes of the study participants will be reassessed by the same evaluator who performed the baseline assessment. Further data will be collected following 24 weeks when Group 2 (the sham group) have also had the chance to experience the treatment and Group 1 (the initial treatment group) have had a 12-week washout. The investigators responsible for collecting all outcome measurements will be blinded to the treatment being administered to the patients.

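### Sustained improvement, the abstract's main efficacy indicator, can be read only at week 24, when no sham control remains and participants and carers can hardly still be blind

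*Protocol article*

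**What the plan says.** The Abstract (Methods and analysis) presents a triple-blinded, placebo-controlled randomised trial of 24 weeks. On the switch it says: "At 12 weeks both placebo and treatment groups will crossover and placebo participants offered the treatment". It then says that the main indicator of clinical efficacy "is evidence of sustained improvements in motor and non-motor symptoms obtained from participant self-reported changes", together with carer report and reassessment by the investigators. It does not define *sustained*.

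The body gives a one-way switch. The last paragraph of the Background speaks of a trial "with a crossover of the placebo group". Trial design gives the sham group active treatment for the second 12 weeks, "while the active treatment group will have a 12 weeks washout period". Intervention says that the placebo group is offered the active helmet. Table 2 arranges the return of helmets at week 12 and provides sham patients with an active one. No section describes a sham helmet for anyone after week 12.

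On timing, Outcome measures says: "Outcome measures will be obtained at baseline, 12-week and 24-week intervals". On blinding, Data collection says: "The investigators responsible for collecting all outcome measurements will be blinded to the treatment being administered to the patients". That sentence directly follows the one on 24-week data and carries no time limit.

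The listed primary outcomes (Table 1 and Primary outcome measurements) are safety, modified MDS-UPDRS Part 3 and PDQ-39. The carer's diary is secondary and qualitative. Statistical analysis counts a participant as improved when the difference between two time points exceeds half an SD, and compares the counts between time points by chi-square. It names no between-group test.

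**The concern.** The headline efficacy criterion falls in the part of the trial that has no control. Improvement that persists to week 24 may reflect the device, expectation, practice on the tests, regression to the mean or a change in background care. A concurrent sham group would separate the device from the rest, and after week 12 there is none.

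The label on the whole 24 weeks invites a reader to treat a week-24 result as blinded and placebo-controlled, which it is not. The authors intend the results to aid the management of patients and the design of a larger trial (Dissemination of results), so a durability claim of this kind would carry weight. In addition, the Abstract's indicator and the list of primary outcomes are two partly different definitions of efficacy. If both stand, either could be given prominence once the results are known.

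**Working it through.** No figure in the protocol bears on this point, so there is none to reproduce. The check sets the sections side by side and then illustrates the size.

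**Step 1: condition by period** (Trial design, Intervention, Table 2, Data collection).

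| Period | Group 1 | Group 2 | Concurrent sham? |
|---|---|---|---|
| Weeks 0–12 | Active helmet | Sham helmet | Yes |
| Weeks 12–24 | No treatment (washout) | Active helmet, offered | No |

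Only Group 2 switches to the other helmet. The Abstract's statement about both groups disagrees with the Background and with Trial design.

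**Step 2: where persistence can be seen.** The visits are baseline, week 12 and week 24. The sham-controlled period holds one post-baseline visit. One visit can show that a difference exists, but not that it lasts. On the scheduled measures, persistence needs week 24.

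**Step 3: who is blind at week 24.** Group 1 has no helmet and knows that it is untreated. Group 2 has accepted an offer of the active helmet. Their carers attend all treatment sessions and Zoom meetings (Inclusion criteria), so they know the same. Two of the three sources of the indicator, self-report and carer report, therefore come from people who know the current condition. Assessor blinding protects only the third source.

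**Step 4: indicator against listed primary outcomes.**

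| Source in the Abstract | Match in Table 1 |
|---|---|
| Participant self-report | PDQ-39 (primary) |
| Investigator reassessment | Modified MDS-UPDRS Part 3 (primary) |
| Carer report | Carer's diary (secondary, qualitative) |
| *Sustained* criterion | None given |

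The mismatch is partial.

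**Step 5: how many would look sustained with no device effect.** The only input from the protocol is the half-SD threshold. The assumptions are:
- normal scores with equal variance at each visit, scaled to a baseline SD of 1;
- the same correlation r between any two visits, 0.6 to 0.9;
- a common placebo or expectation shift s at both follow-up visits, 0 to 0.4 SD;
- 20 per group (40 in two groups);
- *sustained* read as exceeding the threshold at both week 12 and week 24, compared with baseline.

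Each change from baseline has variance 2(1 − r), and the two changes have covariance 1 − r. The share that passes at week 12 is 1 − Φ((0.5 − s)/√(2(1 − r))). For r = 0.6 and s = 0 this is 1 − Φ(0.5/0.894) = 0.288. The share that passes at both visits is the matching bivariate normal tail.

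| r | s (SD) | Week 12 | Both visits | Both, of 20 |
|---|---|---|---|---|
| 0.6 | 0 | 28.8% | 14.8% | 3.0 |
| 0.6 | 0.2 | 36.9% | 21.2% | 4.2 |
| 0.6 | 0.4 | 45.5% | 29.0% | 5.8 |
| 0.9 | 0 | 13.2% | 4.8% | 1.0 |
| 0.9 | 0.2 | 25.1% | 12.1% | 2.4 |
| 0.9 | 0.4 | 41.2% | 24.9% | 5.0 |

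At week 12 the sham group shows how many such responders to expect without the device. At week 24 nothing does.

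**The case against.** The defence has real substance. This is a self-described feasibility study with safety as its primary hypothesis. The body of the article describes the one-way switch consistently, and the Abstract's sentence on both groups is one loose line. *Sustained* is undefined and might mean an effect that holds over the 12 weeks of treatment, for which a sham exists. Two of the three sources match listed primary outcomes. Group 1 after washout can still describe persistence within the group.

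Most of this stands, and it limits the point without removing it. If *sustained* means the treated 12 weeks, the Abstract should say so, and the quantity is then the week-12 comparison proposed below.

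A reader might infer more than the documents support:

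- **That all blinding ends at week 12.** Data collection states assessor blinding without a time limit. It may be fragile when participants and carers know the condition, but the protocol does not give it up.
- **That there is no crossover at all.** The sham group does switch.
- **That a week-24 test between groups would mislead.** If benefit D falls to a fraction k after washout, the expected contrast is kD − D, which is zero for a fully lasting effect. The algebra is right, but Statistical analysis names no such test.
- **That a placebo response would make half of Group 1 responders.** That figure comes only from setting the assumed shift equal to the half-SD threshold.
- **That the rationale for the trial's length fails**, because it speaks of 24 weeks ("suggesting that 24-weeks will be sufficient to demonstrate significant effects") while each person is treated for 12. The same sentence cites significance at 12 weeks in the earlier study, so only its wording is loose.

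**Conclusion.** The point holds in a limited form and should be fixed. Three statements are wrong or inconsistent as written. The 24-week triple-blinded, placebo-controlled label does not fit weeks 12 to 24. The Abstract's crossover of both groups contradicts the body. The main efficacy indicator rests on a persistence that cannot be compared with a concurrent sham. Applied to week 24, the planned responder counts between time points would be an uncontrolled before-and-after reading.

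On the assumptions in the working, about 1 to 3 of 20 participants would look sustained through measurement variation alone, and about 5 to 6 with a 0.4 SD expectation shift. These figures show scale only, because the protocol gives neither r nor s. The structural conclusion does not depend on them. It depends on the absence of any described sham after week 12, which is what the text shows, and on the inference that participants and carers will know whether they are being treated.

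The safety outcome and the week-12 sham comparison are unaffected.

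**What to change.** 1. Define the efficacy conclusion as the active-versus-sham comparison at week 12 on the primary efficacy outcomes already listed, modified MDS-UPDRS Part 3 and PDQ-39. Both stay; choosing one of them would be a preference that this point does not require.
2. In the Abstract, replace sustained improvement as the main indicator with that definition. Carer report remains a secondary, qualitative outcome.
3. State that the sham-controlled, participant-blinded period ends at week 12. Describe the week-24 data as uncontrolled follow-up, reported as change with a confidence interval by group, and say that they support no claim of efficacy or durability.
4. Reconcile the crossover and blinding wording in the Abstract, the last paragraph of the Background, Trial design and Data collection. State whether assessor blinding is meant to hold at week 24.

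These are text changes; visits, measures and treatment stay as they are. The cost is the controlled durability claim, which the design cannot support. Describing within-group persistence in Group 1 remains possible.

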**Clinical Trial Registration:**

[https://www.anzctr.org.au], identifier [12621001722886].

## Background

Parkinson’s disease (PD) is a complex, heterogenous neurodegenerative disorder that presents with both motor and non-motor symptoms (DeMaagd and Philip, 2015). Cognitive decline can be a late manifestation of the disease and as these symptoms usually progress slowly, patients can be living for many years with impaired cognition (Mack and Marsh, 2017). Treatment for PD has often involved multi-modalities including pharmacotherapy, surgical intervention, and physiotherapy (Iarkov et al., 2020). Although significant inroads in PD treatment have been made, to date, optimal treatment for a range of motor, non-motor, and non-dopaminergic symptoms remains a major therapeutic challenge (Hayes et al., 2019).

Consequently, identifying alternative non-invasive, therapeutic methods is needed. Photobiomodulation (PBM) is a non-invasive treatment modality that allows wavelengths of red or near-infrared light to reach tissues beyond the surface of the skin. This therapy has been demonstrated to produce a range of beneficial physiological changes (Heiskanen and Hamblin, 2018). Various light sources, including lasers and light emitting diodes (LEDs) can be applied. PBM therapy (PBMt) was traditionally delivered with hand-held lasers and more recently *via* LED devices, for a wide variety of conditions (Heiskanen and Hamblin, 2018).

To affect the brain using an LED transcranial device, the light must penetrate the skin and reach the tissues of the brain with a sufficient dose to interact with neurons in the brain. The effectiveness of PBMt is therefore dependent on the amount and rate of light energy that can penetrate the human scalp and skull. PBM penetration to the brain has been investigated with results suggesting that near infrared (NIR) light can penetrate to varying depths (Haeussinger et al., 2011; Tedford et al., 2015; Henderson and Morries, 2019; Salehpour et al., 2019). Salehpour et al. (2019), performed a review of the literature and found that on average, penetration of transcranial red/NIR (630–810 nm) is between 0.2 and 10% in humans. In addition, in a cadaver model, transcranial light at 808 nm wavelength has been demonstrated to penetrate the human skull to a depth of 40 mm (Tedford et al., 2015). Haeussinger et al. (2011) described a mean penetration depth of approximately 23 mm. As well, using human cadaver heads (formalin fixed), light has been shown to reach brain parenchyma with the percent penetrance ranging from 12% in the occipital region and 1% in the temporal region (Jagdeo et al., 2012). Used as a proxy for human head, studies on sheep skull showed that at 10–15 W power range, 810 and 980 nm NIR can provide biologically meaningful depth penetration of 30 mm (Henderson and Morries, 2015).

A sleuth of literature exists on the direct effects of PBMt on neuronal cellular metabolism (Hamblin, 2018; Dompe et al., 2020; Hamblin and Liebert, 2022; Wu et al., 2022) with light absorption within the mitochondrial electron transport chain increasing ATP production, leading to a reduction in neuronal death, reduced neuroinflammation, increased cell survival and down regulation of proinflammatory markers.

Specifically, the effect of transcranial LED’s on brain function has been well-studied with changes to various parameters noted in animal models and humans (Shaw et al., 2010; Naeser and Hamblin, 2011; Jahan et al., 2019; Zomorrodi et al., 2019; Longo et al., 2020; El Khoury et al., 2021; Yao et al., 2021). The effects reported in human studies include increased activity in areas associated with attention and novelty (El Khoury et al., 2021), beneficial effects in attentional performance (Jahan et al., 2019), positive effects on modulating brain activity (Yao et al., 2021), increased organization of neural function (Zomorrodi et al., 2019) and a beneficial effect on myelin repair pathways (Longo et al., 2020).

There are also studies that demonstrate improvement in neurological symptoms in patients with PD and other conditions when treated with transcranial PBM. Light therapy in PD has been found to be of clinical benefit in a PD case series (Hamilton et al., 2019). This and other case studies using investigational PBMt devices on neural and cognitive function have presented promising results such as increased energy (Hamblin and Huang, 2019), improved gait and cognition (Saltmarche et al., 2017; Vargas et al., 2017), improved speech, and reduction in freezing episodes (Maloney et al., 2010). A small pilot double blind, placebo-controlled trial (*n* = 11) that examined the effect of transcranial PBMt on mild cognitive dysfunction also reported favorable clinical outcomes (Berman and Nichols, 2019). Recently, Nizamutdinov et al. (2021) demonstrated improvement across several brain functions in dementia patients treated with transcranial LED when compared with a sham treated group. A recent small study on PBMt delivered *via* a transcranial device on PD patients documented its safety and tolerability and demonstrated measurable improvements in several PD related signs and symptoms (Liebert et al., 2021). Transcranial helmet devices appear an ideal solution and an important mode of delivery for PBMt due to ease of self-application and ability to irradiate large area of tissue (Heiskanen and Hamblin, 2018).

The “PDNeuro” Helmet (see Figures 1, 2) allows transcranial application of light at 20 locations, with each location including one infra-red (IR) 810 nm LED and one red 630–670 nm LED. The locations of the “PDNeuro” Helmet LEDs were selected based on anatomic points that have been used clinically and in published studies on neurodegenerative disease (Saltmarche et al., 2017; Hamilton et al., 2019; Liebert et al., 2021). The points include the mastoid process and the second cervical vertebrae points of the sub-occipital region. They are intended to target the corresponding dermatome to permit sensory input to converge onto the trigeminocervical nuclei and the neural connections of the brain stem and cerebellum pathways, including the putative endorestiform nucleus (Bradman and Barry, 2013; Paxinos et al., 2020).

**FIGURE 1 F1:**
[figure not shown]
PDNeuro posterior view.

**FIGURE 2 F2:**
[figure not shown]
PDNeuro lateral view.

This triple blinded, randomized controlled, at-home 24-week trial (RCT) with a crossover of the placebo group, has been designed to test the safety and effectiveness of the “PDNeuro” Helmet device in modifying clinical signs and symptoms experienced by PD patients. This compliments a previous experimental study that showed efficacy of a combined treatment protocol (transcranial with an abdominal, neck, and nasal application) in PD patients (Liebert et al., 2021). In previous published studies, the authors have demonstrated observable changes after 4-weeks of intervention, with statistical significance reported at 12-weeks utilizing both transcranial and remote PBMt, suggesting that 24-weeks will be sufficient to demonstrate significant effects with the present study being a randomized controlled trial with increased total number of participants (Liebert et al., 2021).

### Hypothesis and aims

The main objectives of the study described here are to; investigate the feasibility, safety, tolerability, and efficacy of a novel transcranial LED helmet device (the “PDNeuro” Helmet) and determine the therapeutic effects of PBMt when applied 6 days per week over 12 weeks.

### Hypotheses

1.Primary Hypothesis: Transcranial LED PBMt is a safe, non-invasive therapeutic intervention for patients with diagnosed PD.2.Secondary Hypothesis: Treatment by Transcranial LED PBMt attenuates motor and non-motor symptoms of PD.

## Methods and analysis

### Trial design

The study is a 24-week, two-arm, triple blinded randomized placebo-controlled trial evaluating the safety and effectiveness of the “PDNeuro” Helmet (see Figures 1, 2) compared with a sham helmet device. Treatment will consist of PBMt to the head six times per week for 12 weeks (see Figure 3), with Group 1 (the active group) receiving 12 min of infra-red and 12 min red LED, and Group 2 (the sham group) receiving sham treatment for 24 min. After the initial 12 weeks, the sham patients will be given the active treatment for 12 weeks while the active treatment group will have a 12 weeks washout period and then be re-assessed in 12 weeks (see Figure 3). Outcome measures will be collected by the study investigators that have received specialized training in assessment and data collection.

